## Abstract

**Background:**

The extent of lymph node dissection in colonic cancer surgery remains arguable, and evidence from RCTs regarding extended lymph node dissection outcomes is lacking. This study aimed to compare the long‐term results of D3 lymph node dissection with those of D2 dissection.

**Methods:**

This is a multicentre RCT. The aim is to enrol 768 patients with primary colonic cancer assigned randomly to D2 or D3 lymph node dissection. The trial is assessing the superiority of 5‐year overall survival as the primary endpoint in patients undergoing D3 lymph node dissection *versus* D2 dissection. Secondary endpoints include disease‐free survival, short‐term outcomes (30‐day morbidity and mortality), quality of complete mesocolic excision and lymph node dissection, pattern of lymph node metastasis and quality of life in patients following D2 and D3 lymph node dissection. Experience of 20 D3 and 20 D2 lymph node dissections is required for surgeons to participate in the trial. For surgical accreditation four non‐edited videos of procedures will be assessed. Patients will be followed up for 5 years after last patient enrolment. Intention‐to‐treat analysis will be performed.

**Discussion:**

The results of this study will demonstrate whether extended lymph node dissection is superior to standard dissection in terms of oncological outcomes, and will also assess the impact of more extensive surgery on short‐term outcomes and quality of life.

## Trial registration

1

**Table nlm-table-wrap-1:** 

Primary registry and trial identifying number	Clinicaltrials.gov NCT03009227
Date of registration in primary registry	4.01.2017
Source of material support	National Medical Research Centre of Oncology named after N.N. Petrov
Primary sponsor	National Medical Research Centre of Oncology named after N.N. Petrov
Contact for public queries	[name] [contact]
Contact for scientific queries	[name] [contact]
Title	Multicentre randomized controlled study of oncological outcomes of D3 Lymph Node Dissection in Colon Cancer (COLD)
Countries of recruitment	Russia
Problem studied	Surgical treatment of colon cancer
Interventions	Active control: colon resection with D2 lymph node dissection Active comparator: colon resection with D3 lymph node dissection
Key eligibility criteria	Adult male and female above 18 years old signed informed consent with diagnosed primary colonic cancer. Inclusion criteria: pathologically confirmed adenocarcinoma of colon, TNM – T1‐4aN0‐2 M0‐1 (if metastases are resectable (see 8.2, 10.2)). Exclusion criteria: adjacent organs invasion, non‐resectable distant metastases, acute bowel obstruction, bleeding, tumour perforation (see 8·3).
Study type	Interventional randomized with parallel assignment, non‐blind, phase 3
Date of first enrolment	February 2017
Total sample size	768 patients
Recruitment status	Recruiting
Primary endpoint	Overall survival (5 years after last patient enrolled)
Secondary endpoints	Disease free survival (5 years after last patient enrolled), short‐term outcomes (30 days after operation), lymph node metastases pattern, quality of CME, lymph node yield, quality of life after D2 and D3 lymph node dissections

## Roles and responsibilities

3

### Overseeing the study responsibilities

3.4

**Coordinating investigator:**

Control of the conduct of COLD trial.

Development of protocol and protocol amendments.

Development of Case Report Forms (CRFs).

Arrangements of steering committee meetings.

Preparation and revision of publications.

Study conduct reports preparation.

**Steering committee (coordinating investigator, principal investigators from each centre):**

Maintaining of planned enrolment.

Safety reports review.

Approval of protocol amendments.

Control of quality of study conduct in each centre.

Decision of continuation or termination of the study in centres.

## Protocol synopsis

4

**Table nlm-table-wrap-2:** 

Title:	Multicentre randomized controlled trial of oncological outcomes of D3 lymph node dissection in colon cancer
Study design:	*Patients with primary resectable colon cancer included in the trial are randomized into two groups for D2 (group I) and D3 (group 2) dissection*
Aims and endpoints:	*Aim of the study*: To determine if long‐term outcomes of D3 lymph node dissection in colon cancer are superior to D2 lymph node dissection *Primary endpoint*: Overall survival (time frame: 5 years after last patient enrolment)
	*Secondary endpoints*: Disease‐free survival (time frame: 5 years after last patient enrolment)
	Short‐term outcomes (time frame: 30 days after operation) Lymph node metastasis pattern (number of lymph node with metastases related to number of lymph nodes studied) CME quality (ratio of good, satisfactory and unsatisfactory quality) Lymph node yield (number of lymph nodes removed) Quality of life of patients
**Patients:**	*Male and female patients over 18 years old, who signed informed consent, with diagnosed primary colon cancer T1‐4a N any M 0‐1 (in case of resectable metastases)*
**Number of patients**	*768 (384 + 384)*
**Study duration:**	*The study is conducted starting from January 15 2017 until target number of patient is enrolled and 5 years of follow‐up after enrolment of the last patient*
**Estimated time until target number of patients is reached:**	*3 years*
**Statistical analysis**	*With ά value of 0,05 and β – 0,8, 768 patients enrolment is planned to determine statistical superiority of overall survival after D3 lymph node dissection over D2 dissection with assumed 10% increase in survival with 3 years accrual period and 5 years of follow‐up*

## Background

5

D3‐lymphadenectomy was first proposed in Japanese guidelines for treatment of colon and rectal cancer in 1977^1^. Since that time it has been a surgical standard of care in Japan, China, Korea and Taiwan. It includes complete removal of paracolic, intermediate and central lymph nodes. In right side colon cancer D3‐lymphadenectomy involves removal of all groups of lymph nodes located along the main feeding vessels, which are branches of the superior mesenteric artery (ileocolic, right or middle colic artery). If colon bearing the tumour receives blood supply from branches of inferior mesenteric artery, the removal of lymph nodes located along the trunk of the vessel (the section between the place of origin on aorta and the left colic artery) is essential^2^. This dissection can be carried out precisely along the major vessels and Japanese guidelines do not highlight the need for bowel mesentery excision between embryological layers^3^. Thus, the Japanese guidelines put great emphasis on the level of vessels ligation and lymphadenectomy, but the layer in which the mesentery mobilization should be done is not described in detail.

In Europe, more emphasis is put on the principles of embryology‐focused surgery and on determination of mesentery mobilization layer. The concept of complete mesocolic excision (CME) has aroused much interest as a technique, which can reduce the incidence of local recurrence and increase survival in patients with malignant tumours of the colon. The concept of CME is a sequel of the concept of total mesorectal excision (TME), a recognized and widely used technique in rectal cancer surgery. Implementation of TME into a wide surgical practice has reduced local recurrence rate and increased survival^4^. In TME the dissection is carried along the mesorectal fascia. In CME the layer of surgical dissection lies between the visceral and parietal fascia. So, both techniques are based on principles of embryology‐focused surgery and ensure the idea of en‐bloc resection.

CME concept proposed by Hohenberger et al in 2009 and demonstrated in Erlangen, can be considered as traditional Western approach^5^. According to the method of CME, a key aspect of the operation is sharp and precise division of embryological layers ‐ mobilization of the mesentery along Told's fascia, preserving its integrity and removing all the containing lymph nodes. The level of vascular ligation and groups of lymph nodes to be removed are not clearly defined. Usually CME is performed with CVL (central vascular ligation) ‐ high ligation of vessels. CVL is not an equivalent to D3: feeding vessel may be ligated either at the base, or at a distance of up to 1 cm from the point of origin^6^.

Thereby, the western and eastern concepts of colon resection are similar to a certain extent, but emphasize different aspects of the operation. Japanese approach ‐ D3 lymphadenectomy means high precise definition of lymph node groups to be removed, without mentioning the dissection layer; The European approach ‐ CME, on the other hand, describes in detail the dissection along embryological layers, but does not identify the level of vascular ligation clearly. The main difference is the amount of resected bowel. Comparing specimens from the clinic in Erlangen and from 2 Japanese hospitals revealed that in Japan less colon is resected as well as the number of lymph nodes removed is smaller. This is due to the fact that the Japanese hold the position of ‘economical’ removal of the organ, and the Europeans perform standard hemicolectomies and resection of the colon^7^.

There are various combinations of the above‐mentioned surgical techniques. CME can be combined with any level of vascular ligation, as well as each level of vascular ligation can be complemented by en‐bloc resection following the concept of CME^8^.

Proponents of CME with CVL believe that this method complies with all the principles of oncology, and its main advantage is in the removal of the maximum number of lymph nodes. This contributes to more accurate staging of the disease and the appointment of adequate adjuvant therapy^9^, ^10^. Removal of 28 lymph nodes and more is associated with better survival even in N0 patients^5^. Performing CME helps to remove virtually all of nodal metastases^11^. Fascial envelope damage, on the contrary, leads to deterioration in survival^12^, ^13^. Another advantage of CME is the possibility to standardize the surgical technique of colon cancer treatment and thus improve its quality^14^.

There is a contrary view on the extent of lymphadenectomy. Some authors believe that removal of all mesenteric lymph nodes is unnecessary, and the effect of lymphadenectomy is unproven^15^, ^16^. Some authors proclaim that positive results after CME with the CVL are nothing but a consequence of a good surgical technique^17^. However, expansion of dissection leads to more postoperative complications and functional disturbances than observed after standard resection^18^. For example, high ligation of ileocolic artery can lead to severe diarrhoea; para‐aortic dissection and high ligation of the inferior mesenteric artery may damage the hypogastric plexus and cause sexual dysfunction and urological problems^6^.

Several authors have published data on the significant reduction of local recurrence rate and increase in 5‐year survival after the CME with CVL^5^, ^19^, ^20^, ^21^, ^22^, ^23^, ^24^, ^25^, ^26^, ^27^. No increase in morbidity or mortality was found in these studies. Long‐term results after CME were demonstrated by Hohenberger et al in 2009. Reduction in local recurrence rates from 6·5% to 3·6% was shown. 5‐Year cancer‐related survival improved from 82·1 to 89·1%^5^. However, this data is the result of comparison of patients treated in 1978‐1984 with patients treated in 1995‐2002, which makes it impossible to exclude influence of other factors on the outcome.

Standardization of CME with CVL techniques allowed Bokey et al. to observe improvement in survival rate from 48 to 63% and the cancer‐specific survival from 66 to 76%^26^.

Storli et al. analysed CME outcomes in early colon cancer T1‐2 N0—the overall 3‐year survival after CME was 88·1% (79% in the comparison group), disease‐free survival was 82·1% (79% in the comparison group)^21^.

Kotake et al. were studying outcomes of D3 lymph node dissection in locally advanced colon cancer on the data from Japanese database. It was shown that extended lymph node dissection is associated with increased overall survival and median lymph node yield (21·8 versus 14·9)^28^.

Of interest are the results obtained by Bertelson et al. when comparing a group of patients who underwent CME to those who underwent conventional resection. They showed an increase in 4‐year disease‐free survival for the CME group (85·8 and 75·9%, respectively), but no statistically significant differences were found in overall survival. Increase in disease‐free survival was observed only in patients with stage I and II disease, but not III. They also demonstrated reduction of local recurrence rate after CME (11·3% vs. 16·2% for the comparison group). Multivariate regression analysis showed that CME is an independent predictor of disease‐free survival increase for patients with I ‐ III stages disease.

West et al. used the criteria from the MRC CLASSIC trial to study the plane of mesentery resection for colon cancer. Similarly to the principles of TME evaluation the authors identified three possible planes of dissection: mesocolic, intramesocolic and muscularis propria layer. It was found that only 32% of the dissections were performed in mesocolic layer. They also showed 15% survival advantage for mesocolic plane of resection compared to a muscularis propria plane^12^.

There are at least three ongoing randomized trials studying extent of surgery for colon cancer. LCME trial is comparing lymph node yield after laparoscopic colonic resections with CME vs. D3 lymph node dissection. Mean lymph node count is 20·3 ± 5·8 in CME vs. 19·2 ± 6·7 in D3^29^. Long‐term results are awaited. RELARC trial is researching the hypothesis of superiority of disease free survival after laparoscopic D2 lymph node dissection compared to CME for right colon cancer^30^. SLRC trial is assessing disease free survival after laparoscopic CME vs. D3 lymph node dissection for right colon cancer^31^.

In the studies mentioned there is a certain lack of unity in terminology and concept as in different studies CME is opposed to D2 and D3. In COLD trial the CME is the concept of sharp dissection and is a standard in both groups, while randomization determines the level of vascular ligation. Right and left colon cancers are included, and mini‐invasive or open approach can be used.

Thus, the principles of embryology‐focused surgery and research data underline the need to perform the mesentery resection in the mesocolic layer routinely to improve the results of surgical treatment of patients with tumours of the colon. At the same time the advantages of extended lymphadenectomy (removal of groups of lymph nodes related to the level of D3) are debated. Short‐term and long‐term results of the D3 dissection for cancer colon cancer require further research and comparison to the results of D2 lymphadenectomy.

## Aims of the study

6

### Primary aim of the study

6.1

To determine if long‐term outcomes of D3 lymph node dissection in colon cancer are superior to D2 lymph node dissection.

### Secondary aims of the study

6.2

To determine if there are any differences in disease‐free survival, short‐term outcomes after D2 and D3 lymph node dissections, assess quality of CME, lymph node yield and patients' quality of life.

## Study design

7

### Design

7.1

This is a randomized controlled phase III study, comparing long‐term outcomes of D2 and D3 lymph node dissections in colon cancer. Eligible patients signed written informed consent will be randomized for D2 or D3 lymph node dissection in 1 : 1 ratio.

After in‐hospital treatment postoperative recovery parameters will be evaluated, after that there will be a 5‐year follow‐up period. 768 patients will be recruited in registered centres in Saint‐Petersburg, Moscow and other centres (including other countries if any), registered for the study after patient enrolment had been commenced (up‐to‐date information about centres location can be found on https://clinicaltrials.gov/ct2/show/NCT03009227#contactlocation). Centres are activated after registration procedure (see 9·1). Patients are enrolled via screening procedure and assessing eligibility criteria. To obtain enrolment of planned number of patients additional centres will be initiated and an intensive contact with investigators in each centre will be stimulating desired enrolment.

### Randomization

7.2

Randomization will be performed via main centre (National Medical Research Centre of Oncology named after N.N. Petrov). Eligible patients will be randomized for D2 or D3 lymph node dissection in 1 : 1 ratio for D2 or D3 dissection according to computer generated randomization list created in beforehand^32^.

Information regarding restrictions of randomization to provide groups' homogeneity is located in the document “Mechanism of randomization in COLD trial”, kept in the main centre of the trial concealed from investigators enrolling patients.

Randomization will be performed via sending of randomization list (filled in after patient's enrolment) by electronic message to main centre, where patient will be assigned to a certain line in the randomization list. In reply message investigator receives randomization group and code of the line in the list.

There is no blinding of investigators or patients in current study.

### Endpoints

7.3

Primary endpoint:
Overall survival (time frame: 5 years after last patient enrolment)

Secondary endpoints:
Disease‐free survival (local recurrence or distant metastases during study period)Short‐term outcomes (time frame: 30 days after operation)Lymph node metastasis pattern (number of lymph node with metastases related to number of lymph nodes studied in each lymph node group)CME quality (ratio of good, satisfactory and unsatisfactory quality)Lymph node yield (number of lymph nodes removed)Quality of life of patients

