### Patient enrolment

10.2

Patients are enrolled by investigating physician. Study is discussed with the patient and time and opportunity is given for the patient to familiarize with the informed consent. Patient's consent is confirmed with the signature. After informed consent is signed patient is considered as included in the trial.

For patients with resectable metastases before enrolment treatment plan of metastases removal should be formulated and documented (simultaneous operation or staged procedures). If metastases cannot be resected, such patients are not included in the trial.

Patients meeting all inclusion criteria and having no exclusion criteria are randomized for D2 or D3 lymph node dissection (see 7·2).

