### Follow‐up

10.6

Postoperative follow‐up includes investigations (CT chest and abdomen, colonoscopy) in 6 and 12 month, afterwards annually during the follow‐up period and examinations (or if in‐person contact is not possible it can be substituted by a phone call) in 30 days after surgery and afterwards every 3 month during follow‐up period. During follow‐up period complications, adjuvant treatment and recurrence are registered. Recurrence is registered when local recurrence or distant metastases are found during investigation (Colonoscopy, CT, MRI); serology recurrence is registered if CEA is 3 times higher than baseline. Quality of life will be assessed with validated questionnaires EORTC QLQ‐C30 and colorectal module CR 29 according to *Appendix*
S3 (supporting information).

Patients rejecting surgery after randomization or patients receiving different to randomization group treatment will be analysed in primary randomization groups. For patients rejecting treatment and follow‐up continuation of data collection without treatment is offered.

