## Sample size calculation and statistical analysis

15

To determine the sample size current data from national cancer registry was used^33^, according to which 5 year survival of colon cancer patients is 50%. Survey among surgeons revealed anticipated improvement of survival due to D3 lymph node dissection of 10%. For sample size calculation MedCalc software was used (function of sample size calculation for survival analysis (log rank test) using D. Machin method^34^), according to current survival data, sample size was determined as 762 patients. Using sample size calculation for superiority study via PASS software with C. Chow et al and J. Lachin et al method^35^, ^36^, with α – 0,05 and β – 80%, with 15% of patients lost for follow‐up in case of 3 year accrual period and 5 year follow‐up sample size was determined as 768 patients. As sample sizes obtained by different methods were similar the greater number was used to determine the sample size as 768 patients.

“Intent‐to‐treat” analysis will be performed, thus once randomized patients will be analysed in their randomization group, irrespective of actually received treatment.

For statistical analysis of primary endpoint (overall survival during the study period) Kaplan–Meier method will be implied as the probability of patients survival depends only on time after surgery, as there is no anticipated change of survival during the trial conduct. To compare survival curves long‐rank test will be used.

For secondary endpoints type of analysis will depend on the nature of data. For disease‐free survival (survival without local or distant recurrence during the study period) Kaplan–Meier curves will be used with the long‐rank test. For analysis of short‐term outcomes (morbidity and mortality), lymph node yield parametric and non‐parametric criteria will be used to compare mean values and contingency tables.

For categorical data, to assess the significance of association of two kinds of classification (contingency tables) exact Fisher's test will be implied by default as it can be used when sample distribution is only approximately equal to theoretical distribution and therefore this test is universal. For the final analysis as the sample reaches calculated size Pearson Chi square test will be used.

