Prior to comparing of group mean values in case of quantitative data, a non‐parametrical criterion of Shapiro Wilks will be used to test the normality of distribution. In case of normal distribution Student's criterion for independent samples will be used (dependant samples for quality of life assessment). For data not distributed normally non‐parametric Mann–Whitney U criterion will be implied.

Lymph node metastases pattern will be assessed as calculation of frequency of affected nodes related to number of studied nodes in each group. Correlation analysis of association of size, T‐stage, localization of the tumour with affected groups of lymph nodes, frequency of metastases, tumour budding grade, lymphovascular and perineural tumour invasion. Spearman rank correlation coefficient will be used as the data may be distributed not normally and numeric data may be included. To assess correlation of quantitative data distributed normally Pearson correlation coefficient will be implied.

For the primary endpoint and disease free survival missing data will be handled according to the survival analysis nature – censoring of the patient with the date of last contact.

Missing data for the secondary endpoints will be dealt with by using multiple imputations with Markov chain Monte Carlo method (monotone method if the data shows a monotone pattern of missing values; otherwise, fully conditional specification).

Conclusion of superiority of D3 lymph node dissection will be made in case of statistical superiority of survival during the study of D3 group over D2.

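### Section 7.3 defines disease-free survival by recurrence alone, section 15 words it differently, and no section names death as an event

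*Protocol article*

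**What the plan says.** All references are to the protocol article.

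- **Section 7.3, Endpoints:** DFS is the first secondary endpoint, with the events given as "local recurrence or distant metastases during study period".
- **Section 15, Sample size calculation and statistical analysis:** DFS is worded as "survival without local or distant recurrence during the study period", to be analysed by Kaplan-Meier curves and the log-rank test. For missing data, overall survival (OS) and DFS share one rule: "censoring of the patient with the date of last contact".
- **Section 10.6, Follow-up:** "Recurrence is registered when local recurrence or distant metastases are found during investigation (Colonoscopy, CT, MRI"). It then adds a biochemical category: "serology recurrence is registered if CEA is 3 times higher than baseline".
- **Section 10.2, Patient enrolment:** patients with resectable metastases may enter, provided that a "treatment plan of metastases removal should be formulated and documented (simultaneous operation or staged procedures") before enrolment.

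Death is covered elsewhere. The primary endpoint is "Overall survival (time frame: 5 years after last patient enrolment"). Section 15 also plans a comparison of 30-day mortality, and section 11 has morbidity and mortality reviewed after every 100 enrolled patients.

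**The concern.** DFS is normally read as a composite in which death ends the disease-free period. The event list in 7.3 has no death in it. Under that list a patient who dies without registered recurrence has no event, and the only exit available is censoring. Kaplan-Meier then treats that patient as someone who could still recur later, although death has made this impossible.

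Two things would be at stake. The DFS percentages would be too high and not comparable with those of trials that count death. The D2 versus D3 comparison of DFS would also be blind to any difference in deaths without recurrence. Such deaths are not only other-cause deaths: recurrence is registered from investigations, and section 10.6 allows a phone call in place of an examination, so a patient who dies of cancer before imaging could also contribute no event.

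Two smaller uncertainties concern the same event set. A CEA-based recurrence is registered in 10.6 but appears in neither DFS definition. Patients with metastases at entry who await a staged operation are not disease-free after the index operation, and the recurrence rule in 10.6 makes no exception for lesions already known.

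**Working it through.** **1. The plan's own figures.** The protocol states no figure for DFS. Its sample size is for OS. With hazards -ln(0.5)/5 = 0.139 and -ln(0.6)/5 = 0.102 per year, loss hazard 0.165, accrual of 3 years, follow-up of 5 years and 384 patients per arm, the expected events are 150.1 + 120.3 = 270.4, and power is 0.8004 at one-sided alpha 0.05. This reproduces the printed 270 and 0.8004. None of it depends on how DFS is defined.

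**2. The wordings side by side.** Section 7.3 lists two events and no death. In section 15 the word *survival* may or may not make death a failure. Section 10.6 registers a third kind of recurrence. Two analysts could therefore produce different DFS results from the same data.

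**3. Direction within one arm.** At every time point the recurrence-only curve and the composite curve have the same patients at risk, since both recurrence and death remove a patient. The recurrence-only curve counts the same events or fewer, so it can never lie below the composite. This needs no assumed rate.

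**4. Size within one arm (assumed rates, constant independent hazards).** Let r be the yearly recurrence hazard and d the yearly hazard of death without recurrence.

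- Recurrence-only curve at 5 years: exp(-5r)
- DFS with death counted: exp(-5(r + d))
- True cumulative incidence of recurrence: r/(r + d) × [1 - exp(-5(r + d))]

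| r, d | Recurrence-only | DFS with death | 1 - KM | Cumulative incidence |
|---|---|---|---|---|
| 0.06, 0.03 | exp(-0.30) = 0.741 | exp(-0.45) = 0.638 | 0.259 | (0.06/0.09) × 0.362 = 0.242 |
| 0.08, 0.04 | exp(-0.40) = 0.670 | exp(-0.60) = 0.549 | 0.330 | (0.08/0.12) × 0.451 = 0.301 |

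The level of DFS is overstated by about 10 to 12 points, and the probability of recurrence by about 2 to 3 points.

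**5. Share of events lost (assumed rates).** Take five-year recurrence of 20 to 30%, 30-day mortality of 2% and other-cause death of 1 to 3% per year in the D2 arm. Deaths without recurrence are then about 17 to 44% of first events by five years. For example, with 20% and 1%: r = -ln(0.8)/5 = 0.0446. All first events are 0.02 + 0.98 × [1 - exp(-5 × 0.0546)] = 0.254, of which recurrences are 0.191. The share lost is 0.063/0.254 = 25%.

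**6. Response to operative mortality (illustration only).** Assume a recurrence hazard ratio of 0.85 and 30-day mortality m, so that DFS with death is (1 - m) × exp(-5(r + o)), with o the other-cause death hazard.

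| Assumed 30-day mortality, D3 v D2 | Recurrence-only difference, D3 - D2 | Difference with death counted |
|---|---|---|
| 2% v 2% | +2.7 to +3.8 points | +2.3 to +3.6 points |
| 6% v 2% | +2.7 to +3.8 points | -0.6 to +0.8 points |

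The recurrence-only contrast is the same in both rows. The 6% is a device to show this and is not a figure from the protocol.

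**The case against.** **Censoring of deaths is not stated.** A reader might infer that the plan orders it. It does not. Section 15 can be read as counting death, and the last-contact rule is a rule for missing data that applies equally to OS, where deaths are clearly not censored. This stands. The finding is that 7.3, followed literally, leads to censoring, and that section 15 does not clearly correct it.

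**Staged M1 patients are not said to recur.** It is tempting to say that they count as recurring at the first scan. No section says so, and known lesions with a documented removal plan are not recurrence in the ordinary sense. The protocol gives no M1 share, and such patients can be in both arms, so dilution is more plausible than bias between arms.

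**Operative mortality is not hidden.** It enters OS, the outcomes covered by "For analysis of short‐term outcomes (morbidity and mortality"), and the safety review. It could be missing only from the DFS contrast.

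**A bias in favour of D3 is not shown.** Section 5 speaks of complications and functional disturbance after wider dissection, and reports no increase in morbidity or mortality in the series it cites for complete mesocolic excision with central ligation. The level differences in steps 4 and 5 are for a single arm. A log-rank test that censors deaths is also a recognised test of the cause-specific recurrence hazard, so the test itself is not invalid. What fails is calling it DFS.

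**Such detail belongs in an analysis plan.** That would answer silence. Here the protocol does state the event set, and words it in two ways that do not clearly agree. The argument has more force for baseline metastases, where only a clarification is asked.

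**Conclusion.** The point holds for a secondary endpoint. The DFS event set in 7.3 omits death, the wording in section 15 leaves death open, and 10.6 adds a CEA-based category that neither definition mentions. Applied as 7.3 is written, the analysis is a cause-specific time to recurrence.

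That such a curve cannot lie below DFS follows without assumptions. The size, about 10 to 12 points at five years, rests wholly on the assumed constant, independent hazards, because the protocol gives no recurrence or non-recurrence death rates. Under the same independence, the recurrence-only contrast does not respond to a difference between arms in deaths without recurrence.

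The documents support no statement about the direction or size of a bias between D2 and D3. The 768 patients, the 270 planned events and the superiority conclusion all rest on OS and do not change.

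**What to change.** - **Sections 7.3 and 15:** use one definition. DFS is the time from randomisation to the first of local recurrence, distant metastasis or death from any cause, in all randomised patients.
- **Recurrence alone:** if reported separately, give it as cumulative incidence with death as a competing event.
- **CEA:** reconcile 10.6 with 7.3 and 15 by stating whether a CEA-only recurrence is a DFS event.
- **Baseline metastases:** state that metastases known at entry and planned for staged removal are not recurrence. Add DFS in M0 patients as a sensitivity analysis. Making it the main comparison would drop randomised patients, against the intention-to-treat commitment in section 15.

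**Cost:** a change of wording. Deaths and recurrences are already collected. Reported DFS will be lower, and deaths unrelated to the dissection slightly dilute a pure recurrence effect (+2.3 to +3.6 points against +2.7 to +3.8 in step 6 with equal operative mortality).
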